### Recruitment

Between October 2003 and April 2005, 1005 patients were referred by physicians at four SMMC outpatient clinics located in Menlo Park, Redwood City, South San Francisco, and Daly City. These four clinics were chosen for geographic proximity, accommodating clinic environment, sufficient patient volume, diverse patient demographics, and established adult primary care services. All data acquisition and case management visits took place at the clinic where the patient usually receives his/her primary care.

Physicians at the study clinics were instructed to refer male and female patients between the ages of 35 and 85 who had CHD, CHD risk equivalents (*i.e.*, abdominal aortic aneurysm, peripheral vascular disease, carotid artery disease, or diabetes mellitus), or moderately to severely elevated levels of major CHD risk factors. We were unable to contact 257 of the 1005 referred patients and an additional 142 declined participation (Figure 1). We screened the remaining 596 patients by phone or at the baseline visit and excluded 143 patients for failing to meet the exclusion criteria. These criteria identify patients with circumstances that may severely limit their ability complete the study protocol or that may confound results of the study. The footnotes in table 1 list percentages by exclusion criteria. During the same phone call, those not excluded were scheduled for a baseline visit. Table 1 enumerates study inclusion and exclusion criteria. Consent forms were available in English and Spanish and the patient's informed consent was obtained before the start of the baseline visit. For patients who spoke a language other than English or Spanish, a family member over the age of 18 or a SMMC staff member served as interpreter. As part of the baseline evaluation, biophysical measures were obtained that further excluded 44 patients not meeting inclusion criteria.

**Table 1 T1:** Inclusion and exclusion criteria.

**Inclusion criteria**
The patient has CAD or CAD risk equivalent (abdominal aortic aneurysm, peripheral vascular disease, transient ischemic attack, stroke, diabetes, or FBS ≥ 126 mg/dL × 2) and has at least one of following: SBP ≥ 130 mmHg, DBP ≥ 80 mmHg, LDL ≥ 100 mg/dL, HDL ≤ 40 mg/dL, TG ≥ 150 mg/dL, FBS ≥ 126 mg/dL, BMI ≥ 30, or is a current smoker.
The patient does not have CAD or CAD risk equivalent but has at least one of the following: SBP ≥ 160 mmHg, DBP ≥ 100 mmHg, LDL ≥ 190 mg/dL, TC ≥ 240 mg/dL, TG ≥ 500 mg/dL, HbA1c ≥ 8.0%, BMI ≥ 35, or is a current smoker.
The patient does not have CAD or CAD risk equivalent but has at least two of the following: a) SBP ≥ 140 mmHg or DBP ≤ 90 mmHg, b) HDL ≤ 40 mm/dL or TG ≥ 200 mg/dL, c) LDL ≥ 160 mg/dL or TC ≥ 240 mg/dL, d) FBS ≥ 110 mg/dL × 2, or e) male age ≥ 45 or female age ≥ 55 or with positive family history of CAD.

Abbreviations: FBS = fasting blood sugar, SBP = systolic blood pressure, DBP = diastolic blood pressure, LDL = low-density lipoprotein, HDL = high-density lipoprotein, BMI = body mass index, TC = total cholesterol, TG = triglycerides, HbA1c = hemoglobin A1c.

**Exclusion criteria**
Resident of long-term facility.
Lack of spoken English or Spanish by patient or household member ≥ 18 years old who can serve as interpreter.
Moving before end of intervention (30 months).
Age ≤ 35 or ≥ 85.
Significant comorbidities such as: uncontrolled metabolic disorders (renal failure, liver failure, etc.), active symptoms suggesting acute myocardial infarction or decompensated congestive heart failure, Malignancy or other condition limiting life expectancy, psychiatric disorder with active manifestations.
Substance abuse.
No telephone or means of contacting patient.
Family household member already enrolled.
Homeless and not living with relatives/friends.
Anticipated absence for more than 4 consecutive months.
Difficulty coming to appointments approximately every 1–2 months.
Already participating in the Diabetes program.
Currently pregnant or intends to get pregnant the next 3 years.

**Figure 1 F1:**
[figure not shown]
Enrollment and follow-up in the Stanford and San Mateo County Heart to Heart Trial. ^1^A patient may be ineligible for more thanone reason. ^2^Number of participants who failed to meet exclusion criteria: being resident in long-term facility (n = 1); moving away soon (26); age ≤ 35 or ≥ 85 (13); significant comorbidities (10); substance abuse (2); no telephone (1); family member already enrolled (7); anticipated absence >4 months (18); difficulty coming to appointments (35); participating in other research programs (21); pregnant or planning to become pregnant (2); no English or Spanish and no interpreter (7). ^3^Number of participants who failed to meet inclusion criteria: Has CAD or CAD risk equivalent but did not have any of the CHD risk factors specified in Table 1 (n = 2); does not have CAD or CAD risk equivalent and did not have any of the CHD risk factors specified in Table 1 (n = 42).

### Randomization

A total of 419 patients met all study criteria and provided informed consent. They were randomized into Immediate or Delayed Intervention groups, using the permuted block method stratified by gender and ethnicity (Hispanic vs. Non-Hispanic). A statistician independent of the study generated a sequence of 100 randomization IDs and treatment assignments per clinic for each of the four combinations of gender and ethnicity, *i.e. *1) female, Hispanic, 2) male, Hispanic, 3) female, non-Hispanic, and 4) male, non-Hispanic. An administrative assistant who is not involved in the study printed the IDs and corresponding treatment assignments on separate pages and sealed each page into an opaque envelope. The administrative assistant then placed these envelopes by stratification group and in randomization sequence into four envelope containers for use at each clinic. All case managers were masked to randomization sequence and treatment assignments. At the baseline/randomization visit, each eligible and willing participant was instructed to take the envelope in the very front of the appropriate container, open the envelope in the presence of the case manager, and read his group randomization. The participant would then sign the randomization form and the case manager would record the participant's randomization assignment and the randomization ID number on the randomization disposition form.

Randomization occurred at the patient level in this trial. Randomization at the clinic or physician level would cast detrimental doubts on internal validity of the trial as it would not be feasible to guarantee a balanced distribution of the diversity of clinic sites and physician practice patterns across the study arms. Consequently, it would be difficult to determine whether outcomes reflected the intervention or differences in patient populations across sites and differences in physician practice patterns. A drawback of patient-level randomization is the possibility of contamination. We expect the extent and impact of contamination to be modest, however. By design, study-specific case managers who are independent of existing physician practices within the study clinic sites provide case-management to the intervention patients and the scheduling process is separate from that of the clinical sites. Much of the value of the intervention comes from activities that are not usually given high priority by primary care physicians. In addition, any potential for contamination produces a conservative bias, reducing the measured impact of the intervention and biasing the findings towards the null hypothesis. Furthermore, our statistical methods will specifically address the degree of intra-class correlation within physician's practices and thereby assess the likelihood and potential extent of contamination.

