### Study design

HTH is a 5-year project that consists of a randomized controlled clinical trial in the first 4 years and a transition phase in the last year. The 2-armed clinical trial (Immediate vs. Delayed Intervention) was designed to enroll 400 patients. In an intention-to-treat analysis, this sample size yields 87% power to detect a mean change of 5 points in the Framingham risk score, with an SD of 10, at an α level of 0.01 after accounting for a 25% loss to follow-up.

Participants in both intervention groups continue to receive usual medical care throughout the study period. In addition, participants randomized to Immediate Intervention receive intensive case management for CHD risk reduction for 15 months and then a maintenance program for a minimum of 12 months to assess the durability of initial intervention changes. Participants randomized to Delayed Intervention serve as control for Immediate Intervention patients for the first 15 months and then receive intensive case management for 15 months. The switching-over design not only addresses ethical concerns about withholding treatment from half the study sample, but will also enable us to assess whether the intervention had equal impact whether provided to a naïve population or to a group followed in usual care for 15 months. We will compare change in CHD risk from baseline to 15 months for Immediate Intervention with that from 15 months to 30 months for Delayed Intervention. Similar magnitudes of change in CHD risk between the two study arms would imply that the Delayed Intervention arm was not notably contaminated by the intervention and measurement process and that no noteworthy differences were caused by the 15-month difference in time *per se*.

Immediate Intervention patients who complete their 12-month maintenance period and Delayed Intervention patients who complete their 15-month case management period remain under maintenance case management until they are fully transitioned back to the care of the SMMC in the last year of the project. In addition to patient transition, we will also transition the HTH case management model, as guided by outcomes data from the clinical trial, into an ongoing disease management program operated by SMMC. By including this transition phase, we will be able to assure continuity in patient care and also test the feasibility and effectiveness of implementing our intervention in a community practice setting.

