### Statistical analysis and hypothesis testing

The primary hypothesis of the trial is that Immediate Intervention participants will experience greater reductions in 10-year CHD risk based on Framingham risk probability (primary outcome) than will Delayed Intervention participants. To test the primary hypothesis, we will compare Immediate Intervention participants relative to Delayed Intervention participants in a random-effects regression using SAS PROC GLIMMIX. The dependent variable will be the standardized Framingham risk score at 15-month follow-up. Initially, covariates will be limited to the baseline risk score and intervention status. So we will model participant i (i = 1, 2,..., n_jk_) under the care of physician j within clinic k as:

(1)     Risk_1ijk _= b_0 _+ b_1_Risk_0ijk _+ b_2_Int_ijk _+ α_j _+β_k _+ e_ijk_

where **Risk_1ijk _**is the standardized risk score for the i-th participant at 15 months (time 1) cared for by physician j in clinic k, **Risk_0ijk _**is the risk score at baseline (time 0), **Int_ijk _**is the intervention vs. control status of the i-th participant in the same clinic and under the same physician, **b_0 _**is a constant term, **b_1 _**is the coefficient associated with impact of baseline risk, and **b_2 _**is the coefficient associated with the impact of the intervention. **α_j _**represents the random effect caused by physician j and **β_k _**is the random clinic effect. The error term **e_ijk _**follows normal distribution, N(0, σ^2^). The analysis will be conducted on an intention-to-treat basis. The risk scores of participants lost to follow-up will be set to the baseline or interim values. Alternative methods for handling missing data, such as multiple imputation, may be used if appropriate. Our primary hypothesis will be confirmed if the coefficient associated with the intervention (**b_2_**) is significantly less than 0, implying that the intervention decreased CHD risk scores independent of the baseline level.

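### The physician intra-class correlation can neither detect nor size contamination, so the article should not claim that it will

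*Protocol article*

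**What the plan says.** The Randomization section states that "Randomization occurred at the patient level in this trial" and names contamination as the drawback of that choice. It expects the amount to be modest, because the case managers and their scheduling are separate from the practices. It adds that "any potential for contamination produces a conservative bias, reducing the measured impact of the intervention and biasing the findings towards the null hypothesis". It then closes the argument with a statistical safeguard: "our statistical methods will specifically address the degree of intra-class correlation within physician's practices and thereby assess the likelihood and potential extent of contamination".

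The only model in the article is equation (1), under Statistical analysis and hypothesis testing. It regresses the 15-month standardized risk score on baseline score and intervention status. One term "represents the random effect caused by physician j"; a second is a random clinic effect. On the fixed part the section says "Initially, covariates will be limited to the baseline risk score and intervention status". There is no physician-by-intervention term and no measure of how far a Delayed patient's physician was exposed to the intervention.

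The Study design section plans a different comparison that also bears on contamination: change over months 0–15 in the Immediate arm against change over months 15–30 in the Delayed arm. Its stated reading is that "Similar magnitudes of change in CHD risk between the two study arms would imply that the Delayed Intervention arm was not notably contaminated".

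**The concern.** The sentence in the Randomization section makes the ICC the instrument that measures contamination. An ICC describes how alike the patients of one physician are. Contamination is a shift in the outcomes of one arm. These are different quantities, and the physician intercept in equation (1) applies equally to both arms.

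What is at stake is what the trial may conclude, above all if the effect is small or absent. Read as the article suggests, a small ICC would support saying that contamination was slight when b2 may have been heavily diluted. A larger ICC might be taken for contamination when it reflects only differences between practices.

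**Working it through.** **1. Inputs.** From Study design: planned enrolment (the trial "was designed to enroll 400 patients"), a difference of 5 points, SD 10, α 0.01, 25% loss and 87% power. Not in the article, and so assumed: the number of physicians, patients per physician, the between-physician SD, the share of the effect that spills over, and 1:1 allocation of the 400. The design SD of 10 is taken as the within-physician SD. The article standardizes the score; the ICC does not depend on scale.

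**2. The plan's own figure.** The point does not rest on the power statement, but it fixes the scale of the effect. With 200 per arm, a standard error of 10 × √(2/200) = 1.0, and the effect diluted by 25% loss to 5 × 0.75 = 3.75, two-sided power is Φ(3.75 − 2.576) = 88.0%. This agrees with the stated 87% to within about a point and fits the rule of setting lost patients to baseline or interim values. Counting completers only (150 per arm, undiluted 5 points) gives 96.0%, which does not match.

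**3. Uniform spillover, algebraically.** Let the true effect be δ = −5 and let a share c of it reach every Delayed patient. Leaving out the baseline and clinic terms:

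- Immediate patient of physician j: b0 + δ + α_j + e
- Delayed patient of physician j: b0 + cδ + α_j + e

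The fitted constant becomes b0 + cδ and the fitted intervention coefficient becomes b2 = δ(1 − c). The variance of α_j is untouched, so ICC = σ_α²/(σ_α² + σ²) does not contain c. For c = 0.5, b2 = −2.5; for c = 1, b2 = 0. The ICC is the same in each case. This needs no assumption about the number of physicians.

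**4. Simulation.** The reduced model of step 3, with 40 physicians × 10 patients (5 per arm), SD 10 and 1,500 runs per row:

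| Spillover share c | Physician SD | Mean estimated effect | Mean ICC |
|---|---|---|---|
| 0 | 0 | −5.08 | 0.000 |
| 0.5 | 0 | −2.54 | 0.000 |
| 1 | 0 | 0.01 | 0.001 |
| 0 | 2.3 | −5.00 | 0.050 |
| 0.5 | 2.3 | −2.51 | 0.049 |
| 1 | 2.3 | 0.02 | 0.050 |
| varies by physician (mean 0.5, SD 0.4, cut to 0–1) | 0 | −2.51 | 0.006 |
| varies by physician (same) | 2.3 | −2.49 | 0.055 |

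Uniform spillover can remove the whole effect without moving the ICC. Varying spillover raises it by about 0.005, against a sampling SD of 0.024 to 0.033 for a single trial. The rise enters the same variance term as ordinary physician differences.

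**5. An ICC without spillover.** A between-physician SD of 2 gives 4/(4 + 100) = 0.038, and an SD of 3 gives 9/(9 + 100) = 0.083. The Randomization section itself cites varied physician practice patterns as a reason for randomizing patients, so such values need no spillover to explain them.

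**6. Would an exposure model do better?** Take 200 Delayed patients, SD 10, no physician variance, and regress outcome on the share of the same physician's enrolled patients randomized to Immediate. Patient-level randomization tends to hold these shares near one half, so the value at zero exposure is an extrapolation. Its simulated standard error is about 1.6 (80 physicians × 5), 2.4 (40 × 10) and up to 3.5 (20 × 20). The 95% half-widths are 1.96 × 1.6 = 3.1, 1.96 × 2.4 = 4.7 and 1.96 × 3.5 = 6.9 points, against a 5-point effect.

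**The case against.** Four points can be made for the plan.

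- **The article has another contamination check.** This stands. A reader might infer that nothing is planned, or that a null result could not be interpreted at all. The documents do not support that. A Delayed arm that had already gained from spillover would tend to change less in months 15–30, so the Study design comparison can respond even to uniform spillover. It is indirect and mixed with calendar time, but it exists.
- **The ICC is not wholly uninformative.** This also stands: spillover that differs between physicians does add variance. The addition is small under the assumptions used and cannot be separated from other physician differences, so it gives no usable measure.
- **The article sets no ICC threshold, and its reference to statistical methods is not limited to equation (1).** This is fair as to how the ICC would eventually be reported, and a fuller plan may hold more. But the article itself draws the inference from ICC to contamination, and more detail elsewhere would not make that inference sound.
- **Patient-level randomization does not depend on this sentence.** Correct. It is defended mainly by balance across clinics and practice patterns, by the separation of case managers, and by the direction of the bias. A reader might infer that the primary test is compromised. It is not: the physician intercept remains a proper allowance for clustering.

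**Conclusion.** The concern holds in limited form. For the model given, the ICC cannot detect or size contamination: a small value is not evidence of little contamination, and a large value is not evidence of it. For uniform spillover this is exact and follows from equation (1) alone. The sizes are illustrations only. Half the 5-point effect lost with the ICC unchanged rests on an assumed spillover share. The ICC of about 0.04 to 0.08 without spillover rests on an assumed between-physician SD of 2 to 3 and a within-physician SD of 10. The rise of about 0.005 under varying spillover rests on an assumed 40 × 10 layout. The primary model, estimate and test need no change. What needs correcting is a stated safeguard for interpreting them.

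**What to change.** 1. In the Randomization section, delete the clause that derives the likelihood and extent of contamination from the ICC. Report the ICC only as a clustering adjustment.
2. Base any statement on contamination on the comparison in Study design (Immediate months 0–15 against Delayed months 15–30), and say that it is indirect and confounded with calendar time.
3. Optionally, and as exploratory only, fit a model in Delayed patients of 15-month risk on baseline risk and the share of the same physician's enrolled patients randomized to Immediate. Use the share, because the number also reflects practice volume. Report the slope with a confidence interval. State that it is imprecise, that the value at zero exposure is an extrapolation and not a bound, and that it misses spillover common to all physicians, such as the guideline letter sent to every primary care physician (Delayed intervention section).
4. Do not offer a physician-by-intervention random slope as a test for uniform spillover. Its variance is unmoved by a constant shift, just as the ICC is.

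Items 1 and 2 cost only wording. Item 3 is one extra model on data that equation (1) already indexes by physician.

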### Study measurements

The primary outcome measure is the absolute CHD risk over 10 years. For participants without known CHD, the Framingham risk assessment algorithms published by Wilson et al. [33] will be used to estimate the 10-year risk probability of CHD on the basis of sex, age, systolic blood pressure, total cholesterol (TC), cigarette smoking status, and diabetes status. For participants with existing CHD, their 10-year CHD risk will be extrapolated from 2-year probability estimates [34] after accounting for aging effect and censoring individuals with new-onset CHD as time elapses. Secondary guideline-based outcome measures include low-density lipoprotein cholesterol (LDL-C), high-density lipoprotein cholesterol (HDL-C), systolic and diastolic blood pressure, hemoglobin A1c (HbA1c), physical activity, smoking status, body mass index (BMI), dietary intake of total and saturated fat and fruits and vegetables, use of recommended medications (*e.g.*, aspirin, statins, thiazide diuretics, beta-blockers, and angiotensin-converting enzyme inhibitors [ACEIs]/angiotensin receptor blockers [ARBs]).

Outcome measurements are designed to occur at baseline and 15 months for all patients, at 27 months for Immediate Intervention, and at 30 months for Delayed Intervention patients. HTH case managers, including one nurse practitioner, two registered nurses, and two registered dietitians, completed all baseline measurements, which consisted of biophysical measurements, and lifestyle, social, and demographic questionnaires. Baseline visits were conducted in one or two clinic visits, depending upon patient and case manager schedules.

Height was measured by a wall stadiometer and weight by a digital balance scale. Both of these measures were taken without shoes and while wearing light clothing. BMI was then calculated (in kg/m^2^). Waist circumference (in cm) was measured in standing position using a cloth tape measure placed at the level of the iliac crest. Blood pressure was measured in both arms, using the brachial artery, after 10 minutes of sitting in a relaxed position, and the average of two readings was used. After ascertaining that the patient had fasted for ≥ 12 hours, a finger stick blood sample was obtained for measurement of plasma TC, HDL-C, LDL-C, triglyceride (TG), and glucose levels using the Cholestech LDX point of service testing system (Cholestech Corporation, Hayward, CA). Plasma HbA1c was obtained utilizing the Cholestech GDX.

Patients were asked about medical and family history related to cardiovascular disease (CVD). They were asked to bring all medications, including supplements and nutraceuticals, with them to the baseline visit. Medication name, medication class, dosage, and therapeutic purpose were recorded. Patients with CHD and/or diabetes were specifically asked about their use of β-blockers, statins, ACEIs/ARBs, and aspirin. Health care utilization was assessed by asking about hospitalizations, emergency room visits, and outpatient visits within the past six months.

Case managers recorded patient age, gender, ethnicity (*i.e. *Latinos/Hispanics vs. others including traditional racial categories), education, marital status, employment status, and household size. Standardized questionnaires were administered to collect data on cigarette smoking (short form of stage of change [15]), nicotine dependence for current smokers (Fagerstrom Tolerance Questionnaire [16]), self-perceived health-related quality of life (SF-12 Health Survey [17]), self-reported depression (CES-D scale [18]), fruit, vegetable and fat intake (Block screeners [19,20]), and physical activity (Stanford 7-Day Recall [21]).

All baseline measurements are repeated at two follow-up visits: a first follow-up planned for 15 months and a second planned for 27–30 months. The 15-month follow-up measurements are expected to be completed by August 2006 and the 27–30-month follow-up measurements by October 2007. During follow-up evaluations, case managers continue to collect all biophysical measurements; however, questionnaires are administered by trained research assistants who are masked to treatment assignments. Research assistants also are responsible for calling patients at 7 months and 22 months to obtain interim data on health care utilization.

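### Research assistants described as masked also collect the utilization data that tend to reveal the arm, so masking of the 15-month questionnaires is likely to be lost; the effect on the primary outcome is small

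*Protocol article*

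**What the plan says.** All points are from the Methods of the protocol article.

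- **Masking.** Study measurements says of the follow-up visits: "questionnaires are administered by trained research assistants who are masked to treatment assignments".
- **Second duty of the same role.** The sentence that follows reads: "Research assistants also are responsible for calling patients at 7 months and 22 months to obtain interim data on health care utilization".
- **Content of utilization.** At baseline it covered "hospitalizations, emergency room visits, and outpatient visits within the past six months". The same section says that all baseline measurements are repeated at both follow-up visits, so these items return at 15 months.
- **Place of visits.** Recruitment: "All data acquisition and case management visits took place at the clinic where the patient usually receives his/her primary care".
- **Who receives case management.** Under Study design and Delayed intervention, the Immediate arm has intensive case management for the first 15 months. The Delayed arm has usual care, with case management starting at 15 months.
- **Second follow-up.** Study measurements sets it "at 27 months for Immediate Intervention, and at 30 months for Delayed Intervention patients".
- **Primary analysis.** Statistical analysis and hypothesis testing: "The dependent variable will be the standardized Framingham risk score at 15-month follow-up".
- **What the questionnaires feed.** They collect smoking, diet and physical activity. Smoking status enters the Framingham risk of participants without known CHD. Diet and activity are secondary outcomes, and one secondary hypothesis names diet and exercise changes as the largest mediators.

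**The concern.** The participants know their arm, because each opens the allocation envelope. Masking the interviewer is therefore the article's main safeguard against arm-dependent probing or recording of the self-reported measures. The article then gives the masked role a task whose answers tend to disclose the arm, both seven months after randomization and again at the 15-month visit, where the primary outcome is assessed.

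If an assistant learns the arm, smoking, diet and activity answers may be prompted or coded differently in the two groups. Smoking would carry some of that into the primary outcome. Diet and activity would carry it into secondary outcomes and the mediation analysis. A reader of the results would also credit a protection that the stated procedures do not secure.

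**Working it through.** **1. Do the utilization questions point to the arm?**

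Take the six-month recall described for baseline and assume that the interim call uses it too:

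- The call at month 7 covers months 1 to 7.
- The visit at month 15 covers months 9 to 15.

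Both windows lie wholly within months 0–15, when only the Immediate arm has case management. Those visits take place at the patient's own clinic, so a patient asked about outpatient visits is likely to mention them. No instruction to leave them out is described.

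How many visits would be involved is an assumption. The only frequency given is in an exclusion criterion, "Difficulty coming to appointments approximately every 1–2 months", which concerns ability to attend. The Immediate intervention section says that intensity was individualized. If that frequency were the actual one, six months would hold 6/2 = 3 to 6/1 = 6 visits.

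There are two routes to the primary time point: the 7-month call, if the same assistant later gives that patient's questionnaires, and the utilization items at the 15-month visit itself, if they come before the lifestyle items. The second route needs no overlap with the earlier caller.

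**2. The design figure used as a yardstick.**

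The article plans 400 patients, a difference of 5 points, SD 10, α = 0.01, 25% loss and 87% power. Assume 200 per arm and a two-sided test, with losses kept at baseline values so that the effect is diluted:

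- Diluted effect: 5 × 0.75 = 3.75.
- Standard error: 10 × √(2/200) = 1.0.
- Power: Φ(3.75 − 2.576) = Φ(1.174) = 88.0%; with the noncentral t, 87.7%.

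This agrees with 87% to within about one point. The figure is not in dispute, and 5 points is a fair yardstick.

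**3. Size on the primary outcome, through smoking.**

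Stated inputs: 16% current smokers at baseline and 212 Immediate patients. An even split between arms gives 0.16 × 212 = 33.9, or about 34 smokers.

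Assumed inputs, not in the document: 10–20% of one arm's smokers differentially misreported, and 4–8 risk points per smoker.

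Bias = (smokers misreported ÷ arm size) × points per smoker.

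- Low: 0.10 × 34 = 3.4; 3.4/212 × 4 = 0.06 points.
- High: 0.20 × 34 = 6.8; 6.8/212 × 8 = 0.26 points.

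Against 5 points these are 0.06/5 ≈ 1% and 0.26/5 ≈ 5%.

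Wider assumptions of 10–50% misreported and 3–10 points give 0.16 × 0.10 × 3 = 0.05 to 0.16 × 0.50 × 10 = 0.80 points, or 1–16% of 5. All smokers are counted here, although smoking is documented as an input only for participants without known CHD.

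**4. Diet and activity.** The document gives nothing from which to size an interviewer effect on these measures.

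**5. Second follow-up.** Month 27 occurs only in the Immediate arm and month 30 only in the Delayed arm, so the study month identifies the arm to anyone who knows it. The primary model uses the 15-month score, and that visit is scheduled in the same month for all. The split, like the 22-month call, therefore bears only on durability and on the Delayed arm's change from 15 to 30 months.

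**The case against.** The strongest reply is that this is an article. Call scripts, question order and rosters normally sit in the full protocol. The article does not say that one assistant both calls and interviews the same patient, or that project visits count as outpatient visits. A visit count alone need not identify the arm in a chronically ill cohort, 63% of whom have diabetes.

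That stands against the strong reading, that the assistants cannot stay masked. A reader might infer it, but the document supports only that masking is likely to be lost. It does not dispose of the point, because the point is not missing detail: duties that the article does state work against a property that it also states.

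Three other inferences are tempting and not supported:

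- **That the 27/30-month split biases the primary outcome.** It comes after the 15-month comparison.
- **That case-management visits inflate Immediate-arm utilization and so distort costs.** Under the analysis section, programme cost comes from staff time and usual-care cost from administrative records. Utilization serves only to approximate quality-of-life loss from non-fatal events. No effect on costs is shown.
- **That 3–6 extra visits per six months is a fact of the schedule.** It rests on an eligibility criterion.

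Two further replies also stand. Self-report by participants who know their arm remains however well the interviewer is masked, and standardized instruments give some protection. The larger exposure for the primary outcome is that case managers take the biophysical measurements at follow-up; that is a separate matter.

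**Conclusion.** The concern holds in limited form. Masking of the follow-up interviewers is asserted without a described safeguard against the utilization questions, and it is likely to be lost before or during the 15-month smoking, diet and activity questionnaires.

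The expected effect on the primary outcome is small: about 0.06–0.26 risk points, resting on assumed misreporting of 10–20% and assumed weights of 4–8 points. It would not by itself overturn a 5-point difference. For the self-reported secondary outcomes and mediators the effect is not estimable from the document.

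At the second follow-up the masking claim is not credible for an assistant who knows the study month. That limits only the durability analysis and the Delayed arm's 15–30-month change. The point deserves action because the remedies are nearly free.

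**What to change.** 1. At the 15-month and later visits, ask utilization after all lifestyle questionnaires. This costs only a change of order.
2. Where visits remain to be done, have an existing assistant other than the one who made that patient's interim call give the questionnaires. The cost is a rostering constraint. Recruitment ended in April 2005, so the last 7-month calls fell due about November 2005. The 15-month visits run to August 2006, so this helps only those still outstanding.
3. Add one sensitivity analysis of the 15-month primary outcome with smoking status held at its baseline value. It also removes any genuine cessation effect, so it should be read beside the primary result and not in place of it. The cost is one extra model run.
4. Do not claim masked assessment for the 27/30-month visit.

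Moving the second follow-up to a common month is not advised: months 27 and 30 follow from 15 + 12 and 15 + 15, and a shift would change the period being measured. Nor should patients be asked to leave out project visits when reporting utilization, since that invites the disclosure to be avoided.
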